### Primary outcome measures

#### Neurocognitive Tests

##### California older adult stroop test (inhibition)

Stroop tests assess the ability to suppress a habitual response in favour of an unusual response [33,34]. They generally demonstrate good test-retest reliability (0.90, 0.83 and 0.91 for the three parts of the test) [35] and minimal susceptibility to practice effects [36]. The COAST is a Stroop test developed specifically for use with older populations [37]. Participants are required to first name colours (Colour), then read colour name words (Word); and then name ink colours when the names of colours are printed in a different (non-corresponding/incongruent) colour ink. During the incongruent condition, the two conflicting sources of colour information cause a competing effect (Interference) which is most typically observed as a prolonged reaction time compared to the neutral or congruent conditions [38].

##### Controlled oral word association test (COWAT) (verbal fluency)

Different forms of the COWAT test measure verbal fluency and also draw on executive function and memory. Participants are given one minute to generate as many words as possible that begin with a specific letter. This task is repeated three times with three different letters (e.g. F, A, S). These tests generally demonstrate inter-scorer reliability of 0.70, retest reliability of 0.88 and concurrent validity [39].

##### Letter-number sequencing test (LNS) (working memory)

The Letter-Number Sequencing test [40] measures working memory as well as sequencing, attention and concentration abilities. The participant is read a combination of numbers and letters and is asked to recall the numbers first in ascending order and then the letters in alphabetical order. Each item consists of two trials, and each trial is a different combination of numbers and letters. There are seven items ranging from 2-letter/number sequences (e.g., B-7) to 8-letter/number sequences (e.g., S-2-L-8-B-1-G-7). The maximum score possible is 24 points. The validity and reliability of this test is well established in older adults with test-retest reliability in the range of 0.70 to 0.80 and a factor loading of 0.62 with the Working Memory Index [41].

##### Psychomotor speed (simple reaction time and complex reaction time)

Reaction Time, the time between presentation of a stimulus and initiation of a response, is said to reflect psychomotor and processing speed; and is assessed with 1-choice and 4-choice stimulus conditions. Using computer based testing the first stimulus condition requires identification of a single object (e.g., yellow circle). The second stimulus condition requires the discrimination of a single object, amongst 4 object choices. Simple reaction time (SRT) and 4-choice reaction time (CRT) are calculated as the time (milliseconds) from perception (release of press-pad) to touch of appropriate stimulus on the screen. Split half reliability of up to 0.90 has been reported for an 18 task trial [35]

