**Methods/design:**

This randomised controlled trial involves community dwelling women, without cognitive impairment, aged 65–75 years. Participants are randomised to exercise intervention or non-exercise control groups, for 16 weeks. The intervention consists of twice weekly, 60 minute, exercise classes incorporating aerobic, strength, balance, flexibility, co-ordination and agility training. Primary outcomes are measures of cognitive function and secondary outcomes include physical functioning and a neurocognitive biomarker (brain derived neurotrophic factor). Measures are taken at baseline and 16 weeks later and qualitative data related to the experience and acceptability of the program are collected from a sub-sample of the intervention group.

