## Methods /design

### Study design

The study is a 16-week randomised controlled trial of a multi-modal exercise program for women aged 65–75 years. The study is designed to assess the effect of an exercise intervention combining physical fitness training (aerobic and strength) and motor fitness training (balance, coordination, agility, reaction time and flexibility). Participants are randomly allocated to the intervention group or a no exercise wait list control group (See Figure 1). Measurement of primary and secondary outcomes will take place two weeks prior to commencing the exercise training study (baseline) and within one week of completing the 16 weeks exercise or control period. The protocol has been approved by the Griffith University Human Research Ethics Committee (GU Ref No: PES/05/12/HREC).

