**Phase 3 – Weeks 12-16 – conditioning**						
Cardio (aerobic)	Freestyle aerobics set to music	Antero-postero movements	As for phases 1 and 2 plus:	5-6/10 RPE and 126-128 bpm music	Participant sets own pace as able (increases as able)	Participant sets own pace (decreases intensity or complexity of movement as required)
		Lateral movements	‘Pride of Erin’ dance steps			
		Multiple direction changes	Marching with alternating parallel and 45 degree angle arm movements			
		Increased demands on postural control				
		Higher arm movement				
		Non-isodirectional upper and lower limb movements				
Strength	Circuit	All major muscle groups	Lunges	Recommended RPE = 5-6/10 2x 40 second intervals per station	Increase weight as able	Remove/reduce weight or substitute exercises targeting same muscle group as tolerated
		Compounded exercise	D/b flyes supine on roller Modified (wall) push ups			
Balance	Circuit	Static and dynamic balance	Stand on foam	2x 40 second intervals per station	Introduce perturbation/reduce base of support	One-to-one supervision or remove element (e.g. ball throws)
			Step onto foam and assume one leg pose			
			One legged stand and reach			
Coordination Agility	Free style aerobics + Circuit + Group	Circuit:	Circuit:	Circuit:	Faster movements as able	One-to-one supervision and reduce speed of movement
Reaction time		Dynamic combination exercises	Noodle drops	2x 40 second intervals per station		
		Group:	Group:			
		Dynamic knee lifts in combination with rapid foot movements	Freestyle aerobic routine + noodle			
Flexibility + warm down	Circuit + Group	Circuit: Spinal rotation	Circuit: Alternating wall taps	Circuit:	Increase with musculo-skeletal status	Decrease with musculo-skeletal status
		Group: Static stretches on floor	Group: Cat and camel stretches	2x 40 second intervals per station		
			Lying hamstring stretches			
			Back extensions			
			Quadruplex			

Strength training incorporates progressive weight training and weight bearing exercises involving the major muscle groups. Motor training involves both static and dynamic balance, coordination and agility requiring manoeuvring around and stepping over objects. Reaction time training includes ball activities and flexibility training involves dynamic and static stretches for all major muscle groups (See Table 2). Sessions are conducted by accredited fitness instructors, with a maximum of 20 participants and an instructor-to-participant ratio of 1:10.

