### Outcome measurement

The primary outcome measure is neurocognitive test performance related to the processes of working memory, inhibition, shifting, verbal fluency and simple and complex reaction time i.e. executive function. These functions are highly associated with age-related cognitive decline, mobility and the ability to perform activities of daily living [29-31]. A recent randomised controlled trial of a resistance training program used similar primary outcome measures and demonstrated an effect for a twice a week exercise program [32]. The secondary outcome measures are blood serum levels of BDNF, physical and functional capacity including the 6 minute walk test, the ‘timed up and go’ test and the one-leg stance test of balance; and anthropometric values related to girth circumference at the waist and hip, resting heart rate and blood pressure.

Physical functioning and cognitive assessment are conducted in the community (in halls) by exercise physiologists and psychologists, respectively. Anthropometric measurements are completed by a registered nurse. Cognitive testing requires less than 60 minutes and precedes physical assessment which lasts for 30–40 minutes. Participants are transported to an accredited blood collection facility. Blood samples are then conveyed to a laboratory for assay of plasma Brain Derived Neurotrophic Factor (BDNF).

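### Simple and choice reaction time, both primary, are defined as stimulus to response initiation but calculated from press-pad release to screen touch

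*Protocol article*

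**What the plan says.** The section on psychomotor speed, under the primary outcome measures, opens with a definition: "Reaction Time, the time between presentation of a stimulus and initiation of a response, is said to reflect psychomotor and processing speed". It then describes a computer test with a 1-choice and a 4-choice condition and gives the scoring rule: SRT and CRT "are calculated as the time (milliseconds) from perception (release of press-pad) to touch of appropriate stimulus on the screen".

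The Outcome measurement section places both scores in the primary outcome, which covers "working memory, inhibition, shifting, verbal fluency and simple and complex reaction time i.e. executive function". The abstract keeps cognition and physical function apart: "Primary outcomes are measures of cognitive function and secondary outcomes include physical functioning".

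The intervention includes "motor fitness training (balance, coordination, agility, reaction time and flexibility" (Study design), and the text after Table 2 adds that "Reaction time training includes ball activities". The comparator is a wait list without exercise. No other section gives a different start or end event for SRT or CRT.

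**The concern.** The definition and the scoring rule name different intervals for the same two primary scores. The rule as written times the hand's travel from pad to screen and leaves out the time taken to detect the stimulus and begin to respond.

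This matters more here than in most exercise trials. The trial asks whether a programme with a deliberate motor component improves cognition, and it sets cognitive outcomes as primary and physical ones as secondary. A score made up largely of movement time sits on the wrong side of that divide. It could show a group difference because participants reach faster. It could also show none although participants process the stimulus faster. Neither result would answer the question that the score is meant to answer.

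**Working it through.** The document gives no figure on this point, so the check compares the two intervals. The sample size does not enter.

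**Events in one trial of the test**
- t0: the stimulus appears
- t1: the press-pad is released
- t2: the target on the screen is touched

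**Intervals**
- Definition (stimulus to initiation of the response): t1 − t0. This takes pad release as the initiation of the response, since it is the first overt act in the sequence described.
- Scoring rule (pad release to touch): t2 − t1.
- Total: (t1 − t0) + (t2 − t1) = t2 − t0.

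The defined and scored intervals share only the instant t1. Their overlap is zero.

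**Can the word used for the start event reconcile them?** The rule calls pad release perception. If release marks the end of perception, the clock still starts after the stimulus-to-release time has passed. If perception was meant as stimulus onset, the interval becomes t2 − t0, which still ends at touch and not at initiation. To recover the definition, both the start and the end event have to change.

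**What each score would register.** Suppose exercise shortens pre-release processing by p, the reach by m, and any discrimination that continues after release by r (all in milliseconds; r is about zero for SRT and may be above zero for CRT).

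| Score | Change registered |
|---|---|
| t1 − t0 (definition) | p |
| t2 − t1 (rule as written) | m + r |
| t2 − t0 (total) | p + m + r |

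- Motor gain only (m > 0, p = r = 0): the rule as written shows a gain of m and the definition shows none.
- Gain in pre-release processing only (p > 0, m = r = 0): the rule as written shows none and the definition shows p.

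The document gives no values for p, m or r, so the size of the error cannot be worked out.

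**Share of the primary outcome.** Counting one score each for the Stroop test, verbal fluency, letter-number sequencing, SRT, CRT, and Trail Making parts A and B gives seven, of which two are affected. The count is mine; the protocol states none.

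**The case against.** **It may be a drafting slip.** Perception is an odd name for a hand movement, and the conventional definition stands in the same paragraph. The software is not named, so which interval it exports is unknown. This stands as a limit on the consequence: the harm arises only if the sentence is applied literally. It does not remove the conflict. The article has not left the scoring to a fuller document; it states a start event, an end event and a unit, and these disagree with its own definition.

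**The scores need not be free of cognition.** A reader might infer that the rule captures no decision time at all. The document does not support that. Nothing requires a participant to finish choosing before lifting off, so in the 4-choice task some discrimination may continue during the reach. Zero overlap describes the clock intervals, not the mental content. The argument is strong for SRT and weaker for CRT.

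**No contrast is lost.** A reader might also infer that a planned comparison of 1-choice with 4-choice times is spoiled. The Analyses section plans covariance analysis of follow-up scores and no such contrast.

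**Motor content is admitted, and the training is close to the test anyway.** The measure is headed psychomotor speed, and the Trail Making Test is described as partly motor. Reach speed is never named as a training target; transfer from ball throws and catching dropped objects is plausible but inferred. Because reaction time is itself trained, a correctly scored reaction time would still lie close to the programme's content. All this is fair. But a score with some motor content differs from one whose clock starts only when the movement does.

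**Conclusion.** The point holds as an internal contradiction in the definition of two primary outcomes. As written, SRT and CRT record the interval after response initiation, whereas the protocol defines reaction time as the interval before it. No other section reconciles the two.

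If the rule is applied literally, the scores are wholly or mainly motor for SRT and possibly mixed for CRT. A faster reach could then count as a gain on an outcome labelled executive function, and a gain in pre-release processing could go unrecorded. It would go too far to say that a motor gain will be reported as a cognitive one: that depends on the software's actual output and on transfer from the classes to the reach, and the document shows neither. The size of any bias cannot be computed. The other primary tests are unaffected.

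The conclusion rests on one assumption, that releasing the pad is the initiation of the response. The contradiction should be resolved before the outcomes are analysed, because the possible readings give different primary scores.

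**What to change.** State the start and end event of each score. Score SRT and CRT as stimulus onset to press-pad release, which matches the definition already given. Report press-pad release to screen touch separately as movement time, alongside the motor and physical outcomes.

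If the software stores only onset-to-touch, use that, label it total response time, and acknowledge that it includes a motor component. This fallback is weaker, because a faster reach would still improve the score.

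The cost is one sentence in the protocol and a choice of exported variable, with no new test procedure. This assumes that the software logs both stimulus onset and pad release, which the document does not say and which should be checked first.

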##### Trail making test (TMT) (part A & B) (executive function and shifting)

The TMT is considered to be a test of visual search, attention, flexibility of thinking, motor function, and executive function [34,36,39]. Part B of the TMT requires the individual to mentally shift between two well-rehearsed sequences (numbers and letters) as quickly and as accurately as possible. Shifting ability represents the capacity to adapt to changes in the environment by switching from one mental set to another.

In Part A, the task is to connect the numbers in ascending order (i.e.1-2-3-4…). Part B involves alternately connecting numbers and letters in ascending order (for the numbers) and sequential order for the alphabet letters (i.e. 1-A-2-B…). The score derived for each trail is the number of seconds required to complete the task [39]. Reliability tests for the TMT range from 0.60 to 0.90 [41] and the test is particularly useful for detecting early stages of dementia [41].

### Secondary outcome measures

#### Brain derived Neurotrophic factor (BDNF)

Brain derived neurotrophic factor (BDNF) is a protein and the most abundant neurotrophin in the brain, with an important role in brain neurogenesis, synaptic plasticity, learning and memory [42,43]. The brain has been found to be the main source of BDNF concentrations in venous blood (circulating BDNF) [44]. Participants have their usual breakfast (1–2 hours before venipuncture) and are asked to refrain from exercise for 36 hours prior to blood draw. Eight milliliters of venous blood is drawn into EDTA tubes in the morning, to control for diurnal range variation in plasma BDNF levels [45]. The samples are processed according to the manufacturer’s specifications. Plasma is obtained by centrifugation of blood tubes for 15 min at 2000 × g and 24°C and is aliquoted and stored at −80°C until measured. Plasma samples are assessed for BDNF concentrations using a commonly used [45] commercially available two-site sandwich enzyme-linked immunoabsorbent assay (ELISA) kit (R&D Systems, Minneapolis, MN, USA).

#### Physical functioning: Six minute walk test (6MWT)

The Six-minute walk test is a functional validated measure of aerobic fitness (exercise capacity); and is based on the number of meters walked in six minutes [46]. The 6MWT is performed indoors, along a 30 meter walking course that is flat and straight with a starting line and turnaround point clearly marked. The total distance walked is tallied using pre-marked intervals as a guide. The 6MWT is reported to have strong test-retest reliability when used before and after cardiac rehabilitation programs [47]. A recent study has confirmed that while there is a learning effect that can increase the distance walked; when used as an outcome measure, one measurement is sufficient to show change in performance over time [47].

#### Physical functioning: Timed Up-and-Go

This is a clinical performance based measure of mobility, lower extremities function and fall risk. It is normally distributed, related to executive function and suitable for the assessment of healthy older adults [48]. The TUG test (TUGT) will be conducted using a chair with arms and a seat height of 46 cm placed upon a flat, surface with cones marking the 3 m turning point [49]. Subjects are instructed: “On the word ‘go’, get up and walk as quickly and as safely as possible to cross the line marked on the path, turn around, walk back and sit down”[49]. The activity will be timed from the subject’s back leaving the back of the chair to the return of the subject to this same position. Using a standardised protocol, each subject will be required to perform one untimed, practice TUGT followed by two timed TUGTs (i.e. TUGT1 and TUGT2). At least four minutes of seated rest occurs between each TUGT.

#### Physical functioning: balance test (the one-leg stance test)

The one-leg stance test [50] requires participants to stand unassisted on one leg with hands on hips. Participants are asked to stand on one preferred leg, flex the opposite knee allowing the foot to clear the floor; then balance on the one leg for as long as possible. Timing begins when the leg is lifted and is timed in seconds until the person returns the non-weight bearing foot to the ground. The test has good reliability in older adults (ICC =0.92) [51].

#### Anthropometric measures

Weight is measured using a digital flat weighing scale with a non-slip glass platform. Height (using a stadiometer), waist circumference and hip circumference are measured in centimeters. The waist is measured at the smallest circumference around the torso between the end of the xiphisternum and the top of the iliac crests. The hips are measured at the greatest circumference between the iliac crests and the upper femur. Resting blood pressure is measured using a sphygmomanometer (Welch Allyn 767 Series mobile aneroid sphygmomanometer) and stethoscope. Resting heart rate is calculated by palpation of the radial pulse for one minute. The anthropometric measurements are conducted by a registered nurse.

### Analyses

The data analysis for the randomised controlled trial will be undertaken on an intention-to-treat basis. To characterize the sample in this study, means or proportions and standard deviations (SDs) will be calculated by randomisation group for multiple baseline demographic, cognitive functioning and anthropometric variables. Unadjusted means and SDs for each cognitive performance measure obtained at the baseline and follow-up visits will be calculated. Missing outcome data will be imputed using multiple imputation [52]. Analysis of covariance will be undertaken for 16 week follow-up outcome measure scores, controlling for baseline cognition (TICS), and using baseline outcome values as covariates. Ninety- five per cent confidence intervals and effect sizes (standardised mean differences) will be calculated for each outcome measure. Differences in follow-up secondary outcome measure scores will be assessed for normality of distribution and either parametric or non-parametric statistical analyses applied as appropriate (e.g. ANCOVA, logistic regression etc.). Hierarchical multiple regression analyses will be used to investigate associations between plasma BDNF levels and a range of independent variables including demographic, anthropometric, cognitive functioning and physical functioning variables.

### Qualitative component

A qualitative component is embedded in the study to elicit information about the participants’ experience of the intervention and perception of changes to physical and cognitive function. This component of the study will employ a triangulation approach to the incorporation of qualitative and quantitative data at the stage of results interpretation [53].

Face to face, audiotaped, individual interviews are undertaken with a sub-set of the study population allocated to the intervention group. Interviews are conducted with 12 to 15 participants who give written informed consent. The final number of interviews will be determined by data saturation which will be revealed during concurrent analysis. The interviews commence with questions such as, “Please describe a typical exercise class”, “What aspects of the class did you find most/least enjoyable?” “What aspects of the class did you find least/most beneficial?” “Why?” “What changes if any, have you noticed about yourself that you think may relate to class attendance?” Verbatim transcription of data will be undertaken and thematic analytic techniques will be used to analyse the data [54].

